### 5.5.2 Minor non-compliance (per protocol population)

The Per-Protocol Population (PPP) is defined as the set of subjects without severe non-compliance to the protocol. Minor non-compliance e.g. visit outside the given window, or missing values of marginal importance (stool colour not reported once) are acceptable and do not lead to exclusion from the PPP analysis.

- Minor non-compliance with / Minor Protocol violations (deviations) of the study protocol or instructions
  - subject visit conducted outside of the visit window ( $\pm 3$  days)
  - anthropometric measures were not done in duplicate on some occasion (one or two visits)
  - missing values of minor importance (e.g. stool colour reported not on every diary etc.)

### 5.5.3 Subject drop out

If one or some of the following aspects will occur, subject will be defined as a drop out of the study:

- Lost-to-follow up: Relocation of family
- Withdrawal: Parents / caregivers wish
- Paediatricians recommendations to stop feeding the formula, due to a serious adverse event (incomplete treatment)
- Participation in another clinical trial

Detailed explanation of early drop out should be recorded in the CRF (Withdrawal sheet) with appropriate communication to the monitor.

Please note: if a subject is willing to join the study, but does not fulfil all inclusion criteria or an exclusion criterion applies before randomisation, this is not a drop out. These subjects will be recorded as non-eligible subjects.

## 6 Treatment of subjects

### 6.1 Product description

#### 6.1.1 Composition

The following infant formulae will be used in the study:

1. Intervention Formula: Modified HiPP infant formula with a reduced protein content of 1.89 g/100 kcal and LCPs (arachidonic acid and docosahexaenoic acid, each 12.3 mg/100 kcal = 0.23%).
2. Control Formula: Standard HiPP infant formula with a protein content of 2.2 g/100 kcal, without LCPs. Commercial product.

Both infant formulae are in accordance with relevant EU-directives: for Intervention Formula the Directive 2006/141/EC on Infant Formulae and Follow-on Formulae is relevant. The Control Formula is in accordance with Directive 1999/21/EC. Both formulae are in accordance with Codex Alimentarius standard for Infant Formula.

The infant formulae consist of following ingredients:

##### Ingredients - Modified study formula

Skimmed milk, lactose, partially demineralised sweet whey powder, vegetable oils, LCP-mixture (egg oil, vegetable oils, fish oil), whey protein isolate, calcium chloride, potassium chloride, emulsifier soy lecithin, sodium citrate, L-phenylalanine, vitamin C, manganese carbonate, potassium salts of orthophosphate acids, taurine, L-thryptophan, inositol, iron sulphate, stabilizer L(+)-lactic acid, vitamin E, niacin, zinc oxide, pantothenic acid, copper-lysine complex, vitamin A, vitamin B1, vitamin B6, vitamin B2, potassium iodate, manganese sulphate, folic acid, vitamin K, sodium selenate, biotin, vitamin D, vitamin B12.

##### Ingredients - Standard Study formula (Control formula)

Partially demineralised sweet whey, skimmed milk, vegetable oils, partially demineralised sweet whey powder, lactose, calcium chloride, vitamin C, calcium carbonate, potassium chloride, iron lactate, zinc sulphate, niacin, pantothenic acid, vitamin E, copper sulphate, vitamin A, vitamin B1, vitamin B6, potassium iodate, folic acid, vitamin B2, vitamin K, biotin, vitamin D.

For detailed description of the composition per 100 g powder, per 100 ml ready to drink product and 100 kcal: see Appendix 15.1 and 15.2.

The casein/whey ratio (40% casein, 60% whey) as well as the casein source (skimmed milk) is identically in both formulae.

The vegetable fat mix in the standard formula is composed of: palm oil, rapeseed oil, sun flower oil. This leads to the following fatty acid composition: 36.2% saturated fatty acids, 40.7% monounsaturated fatty acids and 23% polyunsaturated fatty acids (of which are: 90,2% linoleic acid, 9.8% linolenic acid).

The vegetable fat mix in the intervention formula is composed of: palmolein, rapeseed oil, palm kernel oil, sun flower oil. In addition to the vegetable oils, the intervention formula contains a LCP- mixture with the following composition: egg oil, vegetable mix as described above, fish oil. The proportion of fatty acids in the intervention formula is as follows: 35.4% saturated fatty acids, 43.7% monounsaturated fatty acids and 20.9% polyunsaturated fatty acids (of which are: 86,2% linoleic acid, 10.3% linolenic acid, DHA and ARA each 1.1%).

The used infant formulae differ according to following aspects (theoretical values derived from calculation based on the recipe):

|                                | Intervention Formula
(modified)                                                                            | Control Formula
(standard) |
|--------------------------------|-----------------------------------------------------------------------------------------------------------------------|---------------------------------------|
| Energy (kcal/100 g)     | 518                                                                                                                   | 513                                   |
| Protein (g/100 kcal)    | 1.89                                                                                                                  | 2.2                                   |
| Manganese (µg/100 kcal) | 10                                                                                                                    | --                                    |
| Selenium (µg/100 kcal)  | 2.3                                                                                                                   | --                                    |
| Inositol,Taurine        | added                                                                                                                 | --                                    |
| LCPs                    | enriched with arachidonic acid
and docosahexaenoic acid from
fish- and egg-oil
each 0,23% - 12.3 mg/100 kcal | --                                    |

### 6.1.2 Form and dosage

Both infant formulae are available as powder.

The preparation will be carried out as described on the package with the separately provided spoon (Appendix 15.3). 8 of these spoons, put together in a closed envelope labelled with the respective Study Formula Random number, will be provided to the parents together with the formula at Baseline Visit and Visit 2. Separately provided spoons are light blue in contrast to the original dark blue spoons. To make sure that the parents/caregiver used the right spoons usage of light blue spoons will be asked for in the diaries. In addition, the parents/caregivers will be reminded to use these spoons at every Visit and Reminder Call by the investigator.

### **6.1.3 Quality control and shelf life**

Quality control is performed by HiPP at the stage of raw materials, during production and on product release. The shelf life of the product is 15 months (modified study formula) and 18 month (control formula), respectively. A best before date is printed on each package.

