### **6.1.5 Blinding technique**

All study formula will be blinded by the sponsor according to study design. The products will be packed in identical white boxes and labelled with the same product name. The different standard solution is not written on the package - to achieve an equal dosage table, different spoons will be provided for each subject.

The identity of the specific product will be blind to subjects, support staff and investigators.

Formula boxes and spoon packages are marked with specified Study Formula Random Number (chapter 9.6).

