### 8.2 Time schedule

The expected duration of the study will be approximately 26 month. Four months will be needed for preparation of the documents, study organisation and study initiation at study site. At the beginning of June 2009 the first subject will be enrolled in the study. Recruitment of the subjects is estimated to take 12 months (1 year). The latest subject will finish the study 16 month after start of recruitment. After termination of the study, another 6 month will be needed for laboratory analyses, evaluation of the findings and writing the final study report.

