## 9.6 Randomisation

The Study Formula Random Numbers are computer generated to assure an equal and random distribution of study formula to the two different formulas helping to eliminate bias that could be introduced through a selective placement of study formula.

The study formula randomisation will be a permuted-block design to achieve equal numbers in each group. A block size of four will be used. The randomisation is based on sex-specific random list to achieve stratification for gender. The random lists will not be visible to the study personnel involved in recruitment, clinical appointments, sample collection, laboratory analyses and data evaluation.

Study Formula Random Numbers contain 3 digits and are sex-specific:

- Numbers for **girls** start with (uneven hundred number) 101 up to 199 and proceeding with 301
- Numbers for **boys** start with (even hundred number) 201 up to 299 and proceeding with 401

The investigator will receive a list with the ascending Random numbers for boys and girls that shall be followed carefully to assure data meet the assumptions necessary for statistical analysis (Appendix 15.23). If it is decided that the subject will be formula-fed, it will receive the next available study formula random number from the respective sex-specific random list. One by one consecutively Study Formula Random Number has to be given to the subjects. Used Study Formula Random Numbers should be scratched out on the Random number list.

The assignment of the Study Formula Random Number must be documented carefully in the Subject Randomisation List, the Subject Identification List as well as in the individual CRF.

Subjects assigned to the reference breastfeeding group will not receive a Study Formula Random Number; during the course of the study they will only receive a Subject ID Number. Subject ID Number is given to each enrolled subject after informed consent is received.

The Study Formula Random Number will **not** replace the Subject ID Number of the subject. All blood samples and Visit documentation sheets (CRFs) will still be coded by the Subject ID Number primarily. For subjects in one of the formula groups the Study Formula Random

Number will be recorded in addition to the Subject ID Number during all Visits following the randomisation plan ("RANDOM NUMBERB CHART" (Girls/Boys)). At the end of the study the kind of formula given to a subject can be identified with the Study Formula Random Number.

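### The best-before date on each package is left out of the blinding measures, although shelf life differs by arm, so site staff may be able to sort infants by formula

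*Protocol*

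**What the plan says.** Section 6.1.3 gives the shelf life of the two products as "15 months (modified study formula) and 18 month (control formula), respectively. A best before date is printed on each package". It does not say that the date is common to both products or masked.

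Section 6.1.5 sets the standard that the packaging has to meet: "The identity of the specific product will be blind to subjects, support staff and investigators". It says in general that the sponsor blinds the formula, and then lists the means. "The products will be packed in identical white boxes and labelled with the same product name"; the standard solution is left off the label; and separate spoons are supplied. The printed date is not on that list.

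The boxes carry the Study Formula Random Number (6.1.5). Hospital staff hand them out (6.4.1), and parents bring empty boxes back at visits (6.2.3, 8.5.1.8). Section 9.6 uses fixed blocks of four within sex and an ascending number list: "If it is decided that the subject will be formula-fed, it will receive the next available study formula random number". On the length of the supply period, section 8.2 says: "The latest subject will finish the study 16 month after start of recruitment". Section 8.4 allows enrolment to run to a year and a half.

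**The concern.** Section 6.1.5 removes or equalises the features by which the products could be told apart, but section 6.1.3 puts on every package a date that depends on a product-specific shelf life. If the dates differ systematically by arm, staff who see boxes from both arms can sort infants into two groups without breaking any code. The protocol that they work under states which product has the longer life.

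Three things are at stake:

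- **Enrolment.** After day 14, randomisation depends on the investigator's judgement that a full switch by day 28 is feasible (5.1, 8.4). A foreseeable allocation would leave room for selective enrolment.
- **Per-protocol membership.** The per-protocol analysis is primary (9.9), and the site's documentation and classification of feeding compliance decide who is in it (5.5.1, 5.5.2).
- **Safety judgement.** The principal investigator rates how far each adverse event relates to the formula (10.2.1).

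**Working it through.** **Inputs.** Shelf life 15 months (modified) and 18 months (control), from 6.1.3. Planned recruitment 12 months (8.2), at the latest 18 months (8.4). Participation about 4 months. Block size 4 within sex (9.6). Production dates are not given. I therefore write d for the number of months by which the modified formula is made after the control, and show a range. Package is read as the 600 g box.

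**1. Gap between printed dates (control minus modified).** Gap = 18 − (15 + d).

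| d (months, assumed) | Gap (months) |
|---|---|
| −3 | +6 |
| 0 | +3 |
| 1 | +2 |
| 2 | +1 |
| 3 | 0 |
| 6 | −3 |

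For single lots the dates agree only at d = 3. Nothing in the protocol requires that offset.

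**2. Number of lots.** The plan's own figure is reproduced: 12 + 4 = 16 months. The latest case is 18 + 4 = 22 months. Since 16 > 15, one lot of modified formula made at or before the start cannot cover the planned period; at 22 months the same holds for the control (22 > 18). Several lots are therefore likely. That blurs the simple rule that the later date means control, but it does not by itself make the dates agree between arms.

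**3. What readable past allocations are worth.** Take the six equally likely arrangements of a block of four, two per arm, and let staff always guess the arm with more places left (a coin toss if equal). Assume that they know where blocks start and can read earlier boxes in the block.

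| Place in block | Correct guess | Known with certainty |
|---|---|---|
| 1 | 1/2 | 0 |
| 2 | 2/3 | 0 |
| 3 | 1/3 × 1 + 2/3 × 1/2 = 2/3 | 1/3 |
| 4 | 1 | 1 |

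Correct guesses: (1/2 + 2/3 + 2/3 + 1) / 4 = 70.8%, against 50% if blind. Certain: (1/3 + 1) / 4 = 33.3%.

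**4. The direct route.** If the next numbered boxes are already on site, their date could show the allocation without any inference from the block. Section 6.4.1 has formula delivered to the site as required from an outside store. It does not say how far ahead.

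**5. After the fix.** With one common date the gap is 0 for every d, and the date carries no information on the arm.

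**The case against.** The strongest reply is that no arm-specific date is stated. Section 6.1.3 describes a product property and says that a date is printed; it does not say that the dates differ. A sponsor that left the standard solution off the label and supplied separate spoons may well have matched the dates too, and the label text sits in Appendix 15.3, which is listed but not reproduced in the copy at hand. This stands as a reason not to claim that the blind failed. It does not remove the point, because the sections that define the blind leave out a feature that depends on the product.

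It can also be said that recruiting staff cannot see the random lists (9.6) and that Amendment 3 repeats that site personnel had no access to them. That protects the list. It does not protect the box.

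A third reply is that weight is taken on a calibrated scale and repeated (8.5.1.3), so expectation has little hold on the primary outcome. That stands.

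A reader might infer more than the protocol supports:

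- **That every box of every formula infant is marked by arm.** This needs one production date per product, and step 2 suggests several lots. For the same reason, one emergency code break (8.9) need not identify the arm for all date groups.
- **That parents are unblinded.** A parent sees one infant's boxes and has nothing to compare them with.
- **That the supply plan is wrong.** A shelf life shorter than the trial only means more than one lot, and the protocol contains no lot plan to correct.
- **That the investigator chooses the timing of randomisation throughout.** Up to day 14 it follows the parents' decision.

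**Conclusion.** The point holds as a conditional risk to blinding and allocation concealment, mainly through site staff. It does not show that unblinding took place.

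Its size depends on facts that the protocol does not give. The date gap is 3 months if the products are made together, and ranges from −3 to +6 months over the offsets examined, with zero only at an offset of 3 months. If staff can read past allocations, the block of four raises correct guesses from 50% to 70.8%. If they cannot, and the next boxes are not on site, the next allocation stays concealed. No bias in weight gain can be derived from the document.

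The assumptions are full-life dating of both products, a date visible on the box, and no harmonised date in the label appendix. On that footing this is a cheap improvement worth making. The sample size and endpoints are unaffected.

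**What to change.** State in sections 6.1.3 and 6.1.5 that:

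- boxes of both products carry one common use-by date per supply lot, set to the earlier of the two products' dates, or the study label masks the product's own date;
- lot codes do not separate the arms;
- both products are relabelled and replaced together.

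The cost is label text, coordination of lots, and up to 18 − 15 = 3 months of control shelf life given up per lot. If Appendix 15.3 already sets a common date, a cross-reference from 6.1.5 is enough. Amendment 3 shows that the four-month phase is over, so for that phase the sponsor can settle the question by checking whether printed dates or lot codes on the dispensed boxes differed by arm.

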### **6.1.4 Packaging and labelling**

Study formulae are packed in white 600g-paper-boxes. Each box contains two bags (a 300 g) and a measure scope. Four of these paper-boxes are put together in a covering box (4 x 600g-boxes).

Declaration on the 600g-paper boxes is done in English and Serbian (Appendix 15.3). The study formulae are named as “HiPP PRE Infant Milk formula / from birth onwards” / “HiPP PRE Mlečna formula za mladu odojčad / Od rođenja nadalje”.

### **6.1.5 Blinding technique**

All study formula will be blinded by the sponsor according to study design. The products will be packed in identical white boxes and labelled with the same product name. The different standard solution is not written on the package - to achieve an equal dosage table, different spoons will be provided for each subject.

The identity of the specific product will be blind to subjects, support staff and investigators.

Formula boxes and spoon packages are marked with specified Study Formula Random Number (chapter 9.6).

## **6.2 Treatment administration**

### **6.2.1 Amount, dose, frequency**

Parents will receive first formula boxes at Baseline Visit if the infant is randomised at this visit. If not the parents will receive formula boxes after randomisation. Change from another formula or from breastfeeding to fully study formula-feeding must be carried out until beginning of Day 28 (run-in phase). Per definition Day 28 is the latest possible day to fully feed the study formula for the first time. Fully formula feeding must start at that day and then continue until Visit 4 (120 ± 3 days of life).

In case the healthy infant is not breastfed, control formula as well as modified study formula is suitable to be fed from birth onwards.

Study formulae must be given fully as sole nutrition (ad libitum). A feeding guide on the packages will give parents / caregivers advice regarding the average drinking amounts and bottle feeds per day (Appendix 15.3). As this is a guide only a baby may need more or less

than the volumes stated. In this case consultation of the study paediatrician is recommended. The exact amounts consumed will be written down in the diary.

### **6.2.2 Route of administration**

Study formulae will be given in baby bottles (glass or plastic) prepared according to the procedure described on the label (Appendix 15.3).

### **6.2.3 Subject compliance**

The parents / caregivers are asked to bring back all empty formula boxes always to the next visit. For the last Visit (Visit 4) they are asked to bring back the empty and the unused formula boxes. After study termination the formula not used will be destroyed in Belgrade. Date of destruction must be documented in the study formula inventory form.

## **6.3 Concomitant diet and treatment**

### **6.3.1 Concomitant diet**

As defined in chapter 5.4.1 subjects must be fully breast-fed throughout the whole study period (from day 0 to day  $120 \pm 3$  of life) or fully formula-fed latest before day 28 until completion of the study ( $120 \pm 3$  days of life). Partial breastfeeding or feeding with another formula is only acceptable in the formulae groups within the run in period (from birth until Day 27).

Parents are asked, according to national Serbian recommendations and in accordance with ESPGHAN recommendations (ESPGHAN Committee on nutrition: Agostino et al. Complementary Feeding: A Commentary by ESPGHAN Committee on Nutrition; JPGN, 46:99-110, 2008), not to start complementary feeding before the age of 17 weeks (Visit 4).

Minor amounts of unsweetened tea or water are acceptable. Regular feeding of sweetened tea, complementary food, other infant formulae or addition of any kind of supplement to the formula (e.g. lactose, baby rice, cereal) is a major non-compliance with the protocol (see Chapter 5.4 and 5.5).

In any case concomitant diet must be reported in the diaries, the reminder calls and the CRF as “kind of diet”, “frequency” and “amount”.

### **6.3.2 Concomitant treatments / medications**

All concomitant medications / treatments as well as the underlying diseases must be reported in the CRF. Vitamin K, Vitamin D and treatment of reaction on vaccination (suppositories) are permitted. Treatment of mild forms of infections, e.g. mild infections of the respiratory tract treated with inhalation of NaCl-Solution, is permitted.

Antibiotic treatment of the child is an unauthorized treatment with regard to study conduct as well as treatment e.g. with corticosteroid-containing medications. In addition, treatment of

severe infections (e.g. pneumonia, severe diarrhoea with vomiting, requiring hospitalisation > 3 days) is an unauthorized treatment with regard to study conduct.

In any case medication during study conduct must be reported in the Case Report Forms.

## **6.4 Product handling**

### **6.4.1 Distribution and Storage**

All study formula will be supplied by HiPP without charge to the study site and will be stored at *alca trgovina d.o.o.m*, Belgrade. The study formula will be supplied to study site according to need. Supply of study formula must be documented (amount, dated and signed) in the study formula inventory form (Appendix 15.4). Study staff in the hospital will hand out the formula to the parents / caregivers that gave informed consent to participate in the study according to the Study Formula Random Number. Mistakes in the distribution of the formula have to be excluded and accountability must be reported in the Study Formula Accountability Form that is part of the CRF (Appendix 15.12).

During the whole study each subject will receive a total of 24 x 600gr-boxes (= 6 covering boxes) with his or her own specified Study Formula Random Number. At Baseline Visit and Visit 2 they will receive 2 boxes and a separate random number labelled envelope with light blue spoons, and on Visit 1 and Visit 3 they will receive one covering box. In case parents / caregivers ask for more formula, study team has to follow this request and document it in the Study Formula Accountability Form.

If a subject withdraws, no more study formula is dispensed to this subject.

The powder has to be stored at a dry, not too warm place (room temperature) and has to be closed carefully. It has to be used within three weeks after opening the bag.

